## Abstract

**Introduction:**

Foundational preacademic skills are crucial for academic success and serve as predictors of socioeconomic status, income and access to healthcare. However, there is a gap in our understanding of neurodevelopmental patterns underlying preacademic skills in children across low-income and middle-income countries (LMICs). It is essential to identify primary global and regional factors that drive children’s neurodevelopment in LMICs. This study aims to characterise the typical development of healthy children and factors that influence child development in Bahir Dar, Ethiopia.

**Methods and analysis:**

The Bahir Dar Child Development Study is a cross-sectional study implemented in two health centres, Shimbit and Abaymado and in Felege Hiwot Comprehensive Specialized Hospital (FHCSH) in Bahir Dar, Amhara, Ethiopia. Healthy children between 6 and 60 months of age will be recruited from the health centres during vaccination visits or via community outreach. Young children aged 6–36 months will complete the Global Scale for Early Development. A battery of paper and tablet-based assessments of neurocognitive outcomes including visual and verbal reasoning, executive functions and school readiness will be completed for children aged 48–60 months. Caregivers will respond to surveys covering sociodemographic information, the child’s medical history and nutrition, and psychosocial experiences including parental stress and mental health. During a second visit, participants will undergo a low-field MRI scan using the ultra-low-field point-of-care Hyperfine MRI machine at FHCSH. Analyses will examine relationships between risk and protective factors, brain volumes and neurocognitive/developmental outcomes.

**Ethics and dissemination:**

The study is approved by the Institutional Review Boards of Addis Continental Institute of Public Health (ACIPH/lRERC/004/2023/Al/05-2024), Mass General Brigham Hospital (2022P002539) and Brown University (STUDY00000474). Findings will be disseminated via local dissemination events, international conferences and publications.

**Trial Registeration number:**

NCT06648863.

WHAT IS ALREADY KNOWN ON THIS TOPICThe rapid rate of neurodevelopmental growth early in life leaves the brain susceptible to environmental influences, including adverse effects of biological and psychosocial hazards, such as malnutrition, infectious disease, parental stress and depression, and understimulating environments. Early life also presents a window of opportunity, however, where early interventions may be most effective.WHAT THIS STUDY ADDSThis study contributes to the growing body of knowledge regarding brain and neurocognitive development in children in low-resource environments, who have historically been under-represented in research.We will characterise patterns of neurodevelopment in infants and children aged 6–60 months, and examine environmental risks and protective factors that may predict neuroanatomical outcomes in children in Ethiopia.We will generate evidence of associations between objective markers of neural anatomy and child neurocognitive development in children in Ethiopia.We will generate experience to guide the implementation of new technologies and tools to objectively assess neurodevelopment in young children in low resource environments in low and middle-income countries.

## Introduction

 Worldwide, more than 250 million children under 5 years of age fail to meet their developmental potential due to risk factors associated with poverty and food insecurity.^1^ In Ethiopia, 88% of children are exposed to multidimensional poverty, defined as the unfulfilment of rights or needs for basic goods and services, which are inherent risk factors for poor neurodevelopment.^2^ Reduced or impaired neurocognitive development early in life can impact lifelong patterns of cognitive and behavioural development, beginning with early, preacademic skills that are vital to academic success and predictive of later health and socioeconomic standing.^3^ A diverse array of environmental factors that are widespread in low-resource communities can shape children’s neurological and cognitive development. Beginning in fetal development, biological factors such as maternal nutrition, infection and stress can impact fetal neurological development and growth with long-lasting impacts throughout development. Postnatally, maternal and infant nutrition, exposure to disease, environmental neurotoxins, maternal mental health, and parental engagement in psychosocial interaction and stimulation of the infant are some of the factors known to influence developing brain systems and impact emerging cognitive and behavioural functions in children.^4 5^ Most evidence to date comes from Western, industrialised countries, leaving a gap in our understanding of neurodevelopmental patterns in children across low-income and middle-income countries (LMICs) where neurodevelopmentally impactful adversities tend to be magnified. Increased knowledge of risk and protective factors associated with neurodevelopmental characteristics in children can guide targeted interventions to address risk factors that drive poor neurodevelopmental outcomes in children growing up in low-resource environments.^6^

The Bahir Dar Child Development (BCD) study will characterise patterns of typical neurodevelopment in a cross-sectional community sample of children in Bahir Dar, Ethiopia. Data will be harmonised with similar data collected from other countries to provide a global map of child development and identify important targetable factors that will improve neurodevelopmental outcomes in children. The first goal of the study is to examine correlations between brain volumes and neurocognitive/developmental outcomes. The second goal is to examine associations between risk and protective factors and neurodevelopmental outcomes. We will explore these relationships across different age groups. We focus on developmental and neurocognitive outcomes that reflect early developmental milestones in children aged 6–36 months. In older children aged 48 and 60 months, we assess domains that we believe contribute to school readiness, including aspects of visual reasoning, attention, processing speed, verbal development and early literacy, numeracy and early knowledge. Previous studies in LMIC have shown differences in associations of early life exposures and neurodevelopmental outcomes.^7^

## Methods and analysis

### Study design

The BCD Cohort is a cross-sectional observational study designed to characterise typical neurodevelopment in the first 5 years of life in Bahir Dar, Ethiopia.

### Study setting

Bahir Dar is the capital city of the Amhara Region in Ethiopia where the official language is Amharic. The population of Bahir Dar was projected to be 348 429 in 2017.^8^ According to the 2023 United Nations Development Programme multidimensional poverty index, 27% of the Ethiopian population lives below the US$2.15 per day income poverty line.^9^ According to the 2019 Ethiopian Demographic and Health Survey report, 49.8% of women aged 15–49 years in the Amhara region are literate.^10^ Moreover, the rate of stunting among children under 5 years of age is 41.5%.^10^ The study will be conducted in two health centres in Bahir Dar (Shimbit and Abay Mado) and Felege Hiwot Comprehensive Specialized Hospital (FHCSH). FHCSH is the main referral hospital in the region and delivers healthcare services for more than 10 million people in Amhara and neighbouring regions. A Hyperfine low-field (0.064 Tesla) MRI machine was placed in FHCSH on 18 June 2022 and the installation was completed on 1 September 2022.

### Patient and public involvement

Before starting the project, we conducted formative research via key informant interviews with community members, partners, in-laws, religious/community leaders and other relevant stakeholders to develop a community-guided research strategy for introducing low-field MRI in our research. These efforts informed the design and development of educational material for study participants, including videos and the community sensitisation approach. We also consulted with local psychologists, physicians and childcare professionals when developing and testing the assessment battery.

### Study participants and recruitment

The BCD study will enrol healthy children from age 6 to 60 months across eight age cohorts (see table 1). Eligible children will be identified during routine outpatient and vaccination visits at the study health centres. Children who present with clinical symptoms based on parental/child self-report will not be eligible to participate. We will aim to recruit N=50 children into each cohort of the eight cohorts for a total cross-sectional sample size of N=400. Inclusion and exclusion criteria and additional MRI screening questions are shown in table 2.

**Table 1 T1:** Overview of data collection across the cross-sectional cohorts (A–H)

	Enrolment visit		MRI visit
**Cohort**	Assessments	Surveys	Assessments
A/6 monthsB/12 monthsC/18 monthsD/24 monthsE/30 monthsF/36 months	GSED long form (secondary outcome) GSED short form (secondary outcome) Anthropometrics Haemoglobin	Sociodemographic information Home environment Parenting Health history	MRI (Primary outcome)
G/48 monthsH/60 months	Neurocognitive development assessment of reasoning and verbal expression (secondary outcome) Executive functioning (secondary outcome) School readiness (secondary outcome) Anthropometrics Haemoglobin [figure not shown]	Sociodemographic information Home environment Parenting Health history [figure not shown]	MRI (Primary outcome) [figure not shown]

GSEDGlobal Scale for Early Development

**Table 2 T2:** Inclusion and Exclusion criteria

Inclusion criteria	Exclusion criteria
Child lives in Bahir Dar with parents who are willing to travel to FHCSH clinic for the MRI. Family has no plans to move outside of the catchment area in the next 6 months Child is healthy without active clinical symptoms/complaints. The child is within specified age bins for one of the cohort/group±1 months for the 6, 12 and 18 months old and ±2 months for the 24, 36, 48 and 60 months old children.	Child was born with a congenital birth defect or hypoxic ischaemic encephalopathy (birth asphyxia) per maternal report. Child has developmental delay or behavioural disorder per maternal report. Child has clinical signs or symptoms of illness based on maternal and child report (including vomiting, headache or seizures).
Additional screening for MRI scanning	
	Surgical hardware such as staples or screws Metal shrapnel or bullets; Suspected metal in eye; metal jewellery or watch; Metal-containing tattoos or permanent make-up on head or neck.

FHCSHFelege Hiwot Comprehensive Specialized Hospital

### Sample size calculation

The sample size of n=50 children per cohort was selected to ensure collection of at least 30 high-quality MRI per cohort. Expected reasons for data loss include loss to follow-up since MRI is collected during a second visit and poor quality of the images due to movement artefact or incomplete brain visualisation. MRI is an objective quantitative measure; this sample size is widely considered adequate to establish normal population distributions (mean, SD) of brain parameters and brain volumes.^11^

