## Analysis

### Statistical analysis

Descriptive statistics (eg, means and SD, frequencies, and percentages) for key variables will be examined for each cohort. We will use a linear regression approach to estimate associations between exposures and continuous outcomes overall and by cohort. Regression assumptions will be checked and methods such as natural log (ln) transformation may be used to meet normality assumptions. Where appropriate, we will standardise data using relevant reference samples or z-scores created within the sample. We will account for key confounders using a multivariable approach. Baseline characteristics associated with both the outcome and exposure status (p<0.10) will be included in adjusted models as potential confounders.

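### The sample size is justified only for means and SDs, and the planned overall and by-cohort associations need a pooled model that always includes age as the main analysis

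*Protocol article*

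**What the plan says.** The design is descriptive: the study is "designed to characterise typical neurodevelopment in the first 5 years of life in Bahir Dar, Ethiopia" (Protocol article, Study design). The Sample size calculation section states: "The sample size of n=50 children per cohort was selected to ensure collection of at least 30 high-quality MRI per cohort". It lists reasons for data loss but no rate. Its only argument for adequacy is that "this sample size is widely considered adequate to establish normal population distributions (mean, SD) of brain parameters and brain volumes". It gives no precision target, effect size or power.

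The Introduction sets two goals. One reads: "The first goal of the study is to examine correlations between brain volumes and neurocognitive/developmental outcomes". The other concerns associations of risk and protective factors with neurodevelopmental outcomes. Both are worded without reference to cohort, and age-group differences are described as something to be explored.

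The Statistical analysis section uses linear regression to "estimate associations between exposures and continuous outcomes overall and by cohort". Baseline characteristics enter the adjusted models as confounders only if they are related to both exposure and outcome at p<0.10. Age is not named as a fixed covariate.

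Table 1 and Other measures assign different developmental tools by age: GSED in the six cohorts from 6 to 36 months, and another battery at 48 and 60 months.

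**The concern.** The stated rationale answers a different question from the two goals. A size chosen to estimate a mean and SD says nothing about which correlation or regression effect can be seen, pooled or within a cohort. Two things follow.

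- **By-cohort results.** With about 30 scans, a moderate true association will usually be missed. If eight separate cohort results are printed beside the overall one, a reader may take a null cohort as absence of effect, or a difference between cohorts as a developmental pattern.
- **Overall results.** These carry the real information, but they pool children from 6 to 60 months, over which brain size and test scores change greatly. Whether age is in the model depends on a p-value screen, exposure by exposure. An exposure only weakly related to age can fail the screen. Age variation then stays in the residual, and some confounding by age may remain.

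**Working it through.** **Inputs from the article.** 50 children per cohort, eight cohorts, total 400 (Study participants and recruitment); at least 30 usable scans per cohort (Sample size calculation); nominal ages 6, 12, 18, 24, 30, 36, 48 and 60 months (Table 1). **Assumed for the check:** two-sided 5%, 80% power, normal data.

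**The article's own figures.** 8 × 50 = 400 reproduces. 30/50 = 60%, so the plan tolerates up to 40% loss. The 30 has no formula behind it and can be neither reproduced nor refuted.

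**Precision of the mean and SD.**
- n = 30: the half-width for the mean is t(0.975, 29)/√30 = 2.045/5.477 = 0.37 SD. The SD interval runs from √(29/45.72) = 0.80 to √(29/16.05) = 1.34 times the estimate, that is −20% to +34%.
- n = 50, if the phrase on adequacy refers to enrolled children: 0.28 SD, and 0.84 to 1.25.

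**Detectable correlation.** r = tanh[(1.960 + 0.842)/√(n − 3)]. For n = 30: 2.802/√27 = 0.539, and tanh(0.539) = 0.49. In the same way:

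| Analysis | n | Detectable r |
|---|---|---|
| One cohort, scans | 30 | 0.49 |
| One cohort, no scan needed | 50 | 0.39 |
| Brain volumes, all ages | 8 × 30 = 240 | 0.18 |
| Brain–GSED, 6–36 months | 6 × 30 = 180 | 0.21 |
| Brain–older battery, 48–60 months | 2 × 30 = 60 | 0.35 |
| Exposure–GSED, no scan | 6 × 50 = 300 | 0.16 |
| Exposure–older battery, no scan | 2 × 50 = 100 | 0.28 |

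Power in one cohort of 30 scans is 18% at r = 0.2, 36% at r = 0.3 and 60% at r = 0.4. An observed r of 0.3 has a 95% interval of −0.07 to 0.60. With 50 children, power at r = 0.3 is 56%. At this power and level, r = 0.3 needs 85 children in the analysed group.

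**What a pooled model with an exposure-by-age term gains.** Assume a linear change of effect with age, 30 scans per cohort, and the same exposure spread and residual SD in each. The standard error of the effect at age a, relative to a single-cohort estimate, is √{[1 + (a − m)²/v]/k} for k cohorts with mean age m and age variance v.
- All eight cohorts: m = 234/8 = 29.25, v = 9180/8 − 29.25² = 291.9. At 30 months the ratio is √(1.002/8) = 0.35; at 60 months it is √(4.239/8) = 0.73.
- 6–36 months: m = 21, v = 630/6 = 105. At 18 or 24 months it is √(1.086/6) = 0.43; at 6 or 36 months it is √(3.143/6) = 0.72.
- 48–60 months: m = 54, v = 36. The ratio is √(2/2) = 1. With two age groups the term returns the single-cohort estimates, so the gain lies only in the common effect (0.35 against 0.49).

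**Age in the overall model.** The stated rule requires an association with both outcome and exposure. Age will meet the outcome condition easily. For exposures that do not differ much by age it may fail the exposure condition and be left out. If age explains a share R² of the outcome variance, leaving it out multiplies the standard error by about 1/√(1 − R²). The article gives no R², so no figure is put on this.

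**The case against.** Several points on the other side stand.

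- Nothing is miscalculated. This is a thin justification, not an arithmetic error.
- A reader might infer that the two goals are themselves by-cohort and so out of reach. The Introduction does not say so: the goals carry no reference to cohort, age-group work is exploratory, and overall models are already planned.
- A reader might infer that 30 scans fail to deliver the means and SDs claimed. The article sets no precision criterion and its cited source is not at hand. The estimates are loose, and the verb establish is too strong, but the claim is not numerically false. Outer centiles would be looser still, but the article claims only mean and SD.
- A reader might infer that the promise of 30 usable scans is likely to fail. If the true yield were exactly 60%, the chance of at least 30 of 50 would be 56% per cohort and 1% for all eight. But 60% is the floor implied by 30/50, not a stated expectation; at a 75% yield the chances are 99% and 95%. The unstated yield is missing detail, not a shown fault.
- No by-cohort significance test is announced, so the misreading of null results is a risk to guard against, not a stated intention.

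On age, one can answer that it will nearly always pass the screen for brain–outcome correlations, being related to both, and that the article allows z-scores made within the sample or from reference samples, which could remove age. This stands in part. It does not cover exposures weakly related to age, and the standardisation is conditional and not tied to age.

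**Conclusion.** The point holds in limited form. The sample-size rationale covers only the mean and SD of brain volumes and is not linked to either goal. By-cohort associations can show only large effects: |r| of about 0.49 with 30 scans, or 0.39 with 50 children where no scan is needed. Pooled analyses are much better placed, at about 0.18 for exposure–volume associations. Because the tools differ by age, brain–outcome correlations pool only to about 0.21 (GSED) and 0.35 (older battery). The overall model that carries this information is not guaranteed to include age. The figures assume two-sided 5%, 80% power and exactly 30 usable scans per cohort; a higher yield would improve them.

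**What to change.** **Statistical analysis.** Make the main analysis a pooled regression that always includes age, whatever the p<0.10 screen shows, with an exposure-by-age term. Use all ages for brain volumes, 6–36 months for GSED and 48–60 months for the older battery. Centre age within each group so that the exposure coefficient is the effect at the mean age. At 48–60 months, rely on that common effect, since the interaction adds no precision there. Keep the by-cohort estimates, label them exploratory, give confidence intervals, and state that a null result in one cohort is not evidence of no effect.

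**Sample size calculation.** Replace the statement about establishing distributions with the precision obtained: at 30 scans, the mean to ±0.37 SD and the SD to −20%/+34%. Add the pooled detectable correlations above, with the assumed level and power.

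**Cost.** Wording and model specification only; no extra children. The model must assume a form for how an effect changes with age; the linear term is the simplest. The adequacy statement becomes less favourable. A flexible age curve, such as GAMLSS or fractional polynomials, is an option for reference values, not a requirement.

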### Study procedures and data collection

#### Enrolment visit and behavioural assessment

Immediately after the caregiver provides informed consent, the enrolled child will proceed to complete the first visit. Children will undergo a neurocognitive and developmental assessment outlined in and mothers will complete surveys to characterise family sociodemographics, home environment, recent events and hardships, maternal mental health, and child health and nutrition. The protocol for the neurocognitive and developmental assessment varies by age to ensure the use of age-appropriate assessment tools as outlined in table 1. We will also do a finger prick blood test to measure haemoglobin levels.

### MRI visit

Families will travel to FHCSH within 1 month of the enrolment visit to complete the MRI scans.

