## MRI

MRI imaging protocol: MRI data collection will be performed by a trained radiography technologist using the portable, ultra-low field (0.064 Tesla) Hyperfine MRI system (Guilford, Connecticut, USA) installed at FHCSH. We will use the UNITY consortium common protocol which consists of volumetric T1 and T2-weighted imaging and quantitative T2 imaging, optimised for infant/paediatric brain (table 3).^12^ Magnetisation-prepared rapid gradient echo sequences will be used for volumetric T1 imaging, and turbo-spin echo acquisition will be used to attain T2-weighted images.

**Table 3 T3:** The main imaging protocol used in the UNITY studies for children older than 1 month

	Image matrix (X×Y×Z)	Resolution(X×Y×Z) mm^3^	TE/TR/TI (ms)	Time (min:s)
T2 FSE (axial)	112×136×40	1.5×1.5×5	180/2000/NA	2:15
T2 FSE (coronal)	112×44×124	1.5×1.5×5	220/2000/NA	2.22
T2 FSE (sagittal)	36×136×124	1.5×1.5×5	225/2000/NA	2:12
T1 IR-FSE (axial)	112×138×40	1.5×1.5×5	6.6/880/354	6:11
T2 Mapping (optional)	20×18×22	1.7×1.7×5	41, 81, 122, 163, 204, 244, 285, 326, 366, 407/2000/NA	9:22

FSEFast Spin EchoTEEcho timeTIInversion timeTRRepetition time

The protocol for the MRI study visit was developed based on formative work conducted before the study as part of the Longitudinal Infant Development and Growth (LIDG) study.^13^ During the scan, caregivers will be invited to stay in the scanning room to provide comfort and encouragement as needed. Appointments will be scheduled during nap times or when children are anticipated to be tired. Infants and young children will be fed, soothed to sleep and placed in the scanner. Older children who remain awake during the scan will be encouraged to lie still, and a tablet may be used immediately outside the scanner as a distraction. Earplugs will be placed prior to scanning to prevent startling or awakening during the scan. The sequences take around 35 min to complete. Scans will be repeated up to two times if movement or image artefacts are significant during live monitoring of the scan quality. A clinical read/interpretation of the MRI will be done by senior radiologists at FHCSH within 1 week of the scan. Incidental findings will be communicated to the family along with a plan for referral. The primary MRI outcome will be total supratentorial brain volume. We will also assess ventricular, Cerebrospinal Fluid (CSF), and thalamus volumes.

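### Cohort age is fixed at enrolment, but brain volume is measured up to a month later and the analysis does not secure age at scan

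*Protocol article*

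**What the plan says.** Age is an inclusion criterion in Table 2 (Study participants and recruitment): "The child is within specified age bins for one of the cohort/group±1 months for the 6, 12 and 18 months old", with ±2 months for the 24-, 36-, 48- and 60-month groups. As an inclusion criterion it is judged when the child enters. Table 1 places the developmental and neurocognitive assessments at that enrolment visit and the MRI at a separate one. The MRI visit section gives the interval: "Families will travel to FHCSH within 1 month of the enrolment visit to complete the MRI scans". No age limit is attached to the scan date.

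The scan carries the main result: "The primary MRI outcome will be total supratentorial brain volume". The Sample size calculation section says "The sample size of n=50 children per cohort was selected to ensure collection of at least 30 high-quality MRI per cohort" and argues that "this sample size is widely considered adequate to establish normal population distributions (mean, SD) of brain parameters and brain volumes".

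The Statistical analysis section plans descriptive statistics for each cohort and continues: "We will use a linear regression approach to estimate associations between exposures and continuous outcomes overall and by cohort". Covariates are baseline characteristics related to both outcome and exposure at p<0.10. Standardisation to reference samples or within-sample z-scores is allowed where suitable, with no age basis given. Age at scan is not named.

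**The concern.** The sample size is justified by the wish to describe the mean and SD of brain volume at given ages, and the Introduction says the data will be harmonised with data from other countries. For that purpose the age that matters is the age when the image is taken. The protocol controls a different age, the one at entry, and the gap between the two can only add age. A child who enters at 7 months and is scanned a month later contributes an 8-month brain to the 6-month summary.

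The study's first goal, correlating brain volume with development, is also touched. Development is measured at enrolment and volume 0 to 1 month later. Within a cohort both measures depend on age, so part of any correlation comes from shared age, and the varying interval adds noise.

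The stated adjustment rule does not reliably deal with this. Age at scan is not a baseline characteristic in the usual sense. Within one cohort it may be unrelated to the exposure, and would then fail a screen that requires association with both exposure and outcome, however strongly it predicts volume.

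**Working it through.** **The plan's own figures.** 8 cohorts × 50 = 400, which agrees with "We will aim to recruit N=50 children into each cohort of the eight cohorts for a total cross-sectional sample size of N=400". At least 30 usable scans from 50 children implies a yield of 30/50 = 60%. The point does not rest on either figure.

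**Inputs from the protocol.** Entry window w = 1 month (6-, 12- and 18-month cohorts) or 2 months (24-, 36-, 48- and 60-month cohorts). Delay from entry to scan: 0 to 1 month. Table 2 gives no window for the 30-month cohort, so it is left out.

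**Possible age at scan** runs from (nominal − w) to (nominal + w + 1).

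| Cohort (months) | Age at entry | Possible age at scan |
|---|---|---|
| 6 | 5-7 | 5-8 |
| 12 | 11-13 | 11-14 |
| 18 | 17-19 | 17-20 |
| 24 | 22-26 | 22-27 |
| 36 | 34-38 | 34-39 |
| 48 | 46-50 | 46-51 |
| 60 | 58-62 | 58-63 |

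**Distribution of age at scan.** Assume entry age uniform over the window, delay uniform over 0-1 month, and the two independent. The protocol gives none of this.

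- Mean age at scan = nominal + 0.5 month.
- Share above the upper limit = mean delay / (2w) = 0.5/2 = 25% for w = 1, and 0.5/4 = 12.5% for w = 2.
- SD of age for w = 1: √(4/12) = 0.58 month at entry and √(4/12 + 1/12) = 0.65 month at scan.

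**Effect on the 6-month mean.** Growth per month g and between-child SD are assumptions, with SD = 8% of mean volume. Shift in SD units = 0.5 × g / 8%.

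- g = 2%: 0.5 × 2/8 = 0.13
- g = 3%: 0.5 × 3/8 = 0.19
- g = 5%: 0.5 × 5/8 = 0.31

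The standard error of a mean of 30 is 1/√30 = 0.18 SD, so the shift is about 0.7 to 1.7 standard errors. A mean delay of 0.25 month would halve it, to 0.06-0.16 SD.

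**Effect on the 6-month SD.** The SD with the window alone is √(8² + g² × 4/12); with window and delay it is √(8² + g² × 5/12). For g = 3% these are 8.19 and 8.23, an increase of 0.6% (from unrounded values). For g = 5% they are 8.50 and 8.63, an increase of 1.4%. The delay barely affects the spread.

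**The case against.** The best reply is that a short interval between two visits is ordinary, is openly stated, and does harm only if volumes are summarised by nominal cohort with scan age ignored. An analysis plan that is not shown may use exact age, and the Statistical analysis section allows standardisation and covariates. That limits how hard the point can be pressed. It does not remove it, because the article itself states a covariate rule, and that rule gives no assurance that age at scan will enter.

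Several stronger readings are tempting and are not supported.

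- *That the 6-month volumes are not at the age the cohort states.* The cohort is 6 ± 1 months, so scans at 5-7 months are as stated. Under the assumptions above, 75% of scans in the ±1 month cohorts stay at or below the upper limit.
- *That every cohort mean is biased towards an older age.* This needs entry ages centred on the nominal age, which the protocol does not establish. If children entered on average half a month early, a mean delay of half a month would bring the mean scan age to nominal.
- *That age alone separates children in the 6-month cohort by up to 1.9 SD.* This is 3 months × 5% / 8%, and two of those three months are the declared entry window.
- *That the bins ignore prematurity.* The article does not say whether age is chronological or gestation-corrected. A condensed article's silence on this is not a finding, and it has no bearing on the 5-8 month range.
- *That the window must be enforced at the scan date.* A child entering near 7 months would then have almost no time to be scanned, and the Sample size calculation section already expects losses before the second visit.

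**Conclusion.** The point holds in a limited form. It follows directly from the protocol that the age window applies at entry, that the scan may come up to a month later, and that scans in the three youngest cohorts can fall up to a month above their stated upper limit. The 0.5-month mean excess and the 25% share rest on assumed uniform, centred entry ages and a uniform delay. The 0.13-0.31 SD shift in the 6-month mean also rests on assumed growth of 2-5% per month and an assumed SD of 8%. If these are about right, the shift is of the same order as the standard error of the cohort mean, so it is worth removing from a reference value but would not overturn the study. The effect on the cohort SD is negligible. What needs changing is the analysis text, more than the visit schedule.

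**What to change.** In the Statistical analysis section:

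- Name exact age at scan as a fixed covariate in every model for brain volume, outside the p<0.10 screen, and report cohort means at, or standardised to, the nominal age.
- Name exact age at assessment in the same way for GSED and neurocognitive scores.
- In the brain-development correlations, include both ages, or one age and the interval. These are equivalent, since age at scan is age at assessment plus the interval; all three cannot enter together.
- Report the achieved age at scan for each cohort (mean, SD, range and number outside the window).

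Where feasible, book scans for the youngest cohorts promptly after enrolment.

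The cost is mainly wording, since the ages follow from birth and visit dates. There is also a small statistical price. If the age slope is estimated within one cohort of 30 and the mean is moved back by 0.5 month, the standard error grows by a factor of about √(1 + 0.5²/0.65²) = 1.26, from 0.18 to about 0.23 SD. Estimating the slope from an age curve fitted across cohorts would reduce this price and is the better choice.
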